#### Exclusion criteria

2.2.2

Presence of gastrointestinal diseases;Use of antibiotics or dietary supplements containing probiotics or prebiotics in the last 15 days;Pregnancy

### Interventions

2.3

Participants will be instructed to take a sachet before breakfast, in the form of mix or powder in water and drink, and to store the sachets at room temperature. To improve adherence to the treatment, messages will be sent and/or phone calls made to verify that participants are following the protocol correctly and that these are working as intended. During the clinical trial, the use of laxatives will be prohibited.

The study is composed by 3 parallel arms:

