#### Inclusion criteria

2.2.1

Patients eligible for the trial are adults aged 20 to 80 years;Clinical diagnosis of functional constipation according to Rome IV. The Rome IV Consensus defines functional constipation as a dysfunction that manifests with difficult, infrequent and incomplete bowel movements. The constipation must have started 6 months previous and become more frequent in the last 3 months, including 2 or more of the following characteristic: involving <25% of bowel movements: effort, hardened resistance (Bristol scale 1–2), feeling of incomplete removal, sensation of anorectal obstruction, digital manoeuvres to facilitate the exit of fecal content, less than 3 spontaneous bowel movements/week and need for laxatives^[4]^;Granting of written informed consent.

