#### Primary outcomes

2.4.1

Changes in the frequency of bowel movements and in stool quality will be noted down in a table which the patient must fill out with information about daily frequency and type of stool (on a scale of 1–7 of the Bristol scale, or whether there was no bowel movement).

Stool form will be assessed using the BSFS (Bristol Stool Form Scale), a simple tool for estimating intestinal transit time.^[5]^ The BSFS classifies stools into 7 categories, including type 1, separate hard lumps, like nuts; type 2, sausage-shaped, but lumpy; type 3, like a sausage but with cracks on the surface; type 4, like a sausage or snake, smooth and soft; type 5, soft blobs with clear-cut edges; type 6, fluffy pieces with ragged edges, a mushy stool; type 7, watery, no solid pieces.^[5]^ These types are categorized into slow transit (types 1 and 2), normal transit (types 3–5), and fast transit (types 6 and 7).

The metric of analysis will be the comparison between 0 and 30 days, considering that the number of effective bowel movements over 4 times a week is an effective value for the treatment and the quality of the stools from 3 to 5.

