### Data analysis planning

2.10

Preliminary data indicate that the number of evacuations weekly is 2 or 3 times higher in patients than in control volunteers. The hypothesis is that treatment will likely increase the number of weekly bowel movements from 1 to 3 times to over 4 times a week, while no changes will be seen in the placebo group.

Anova will be used in order to compare continuous variables between the intervention and control groups. Score changes between the intervention and the control groups will be compared by Kruskall–Wallis.

Analysis of adverse events (if any) and the other outcomes will be performed using the Student *t* test and Mann–Whitney *U* test. In all measured will used the intention to treat analysis. The level of significance will be at *P* < .05. The raw data will be input into the statistical software. Statistical analysis will be performed at STATA v.14.2.

All data collected on paper will be marked with a research identification number to avoid identifying the participants and stored in a locked cabinet. Only the author of the research report can access these identified data sets.

The data monitoring committee is not necessary because the statistical analysts will be blind to evaluate the outcomes data.

Volunteers will be instructed to write down any adverse events on the attached form A and if they feel the need to interrupt treatment due to inconvenience that they are unable to continue and write down what the reactions were.

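### Laxatives are banned during the trial but not restricted before day 0, and the primary outcome does not single out spontaneous movements, so in laxative users the day 0 to day 30 change mixes withdrawal with product effect

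*Protocol article*

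**What the plan says.** All references are to the protocol article.

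- **Section 2.2.1 (inclusion).** The list of Rome IV features, of which two or more are needed, ends with "less than 3 spontaneous bowel movements/week and need for laxatives". Current laxative users can therefore enter, and entry is judged on *spontaneous* movements.
- **Section 2.2.2 (exclusion).** The only pre-entry product restriction is "Use of antibiotics or dietary supplements containing probiotics or prebiotics in the last 15 days". Laxatives are not listed, and the article states no run-in.
- **Section 2.3 (interventions).** "During the clinical trial, the use of laxatives will be prohibited". The rule applies to every arm.
- **Section 2.4.1 (primary outcomes).** The patient's table holds "information about daily frequency and type of stool". "The metric of analysis will be the comparison between 0 and 30 days", and the success value is that "the number of effective bowel movements over 4 times a week is an effective value for the treatment". The word *effective* is not defined, and *spontaneous* is not used.
- **Section 2.10 (analysis).** The hypothesis is that treatment will "increase the number of weekly bowel movements from 1 to 3 times to over 4 times a week". On the comparator side, the assumption reads "while no changes will be seen in the placebo group". Comparisons are between groups, by intention to treat.

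**The concern.** For a patient taking laxatives at enrolment, the two ends of the primary comparison can be measured under different conditions: assisted at day 0, unassisted at day 30. Suppose such a patient has 4 assisted movements a week at day 0, would have 2 without laxatives, and reaches 3 on the product. The product has added 1, but the recorded change is −1.

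Three things are at stake:

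- the meaning of the 0-to-30-day change and of reaching the over-4-per-week value in laxative users;
- the precision of the between-arm comparison;
- the planning assumption that the placebo arm stays flat.

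A separate question is what happens when a patient breaks the ban. Nothing in the stated outcome removes the resulting movements from the count.

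**Working it through.** **Step 1. The laxative condition at each time point.**

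| | Before or at day 0 | Day 30 |
|---|---|---|
| Laxative rule | none stated (2.2.2 omits laxatives) | prohibited (2.3) |
| Movements named | *spontaneous*, for entry (2.2.1) | frequency of movements; *effective*, undefined (2.4.1) |

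The sections do not place both measurements under a stated common condition, and the outcome wording does not make up for it.

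**Step 2. The plan's own sample size.** Section 2.5 gives 44 per group, 132 in total, and 152 after 15% dropout. 132 × 1.15 = 151.8, so 152 is reproduced by multiplying by 1.15. The 44 cannot be reproduced, because section 2.5 gives no means or SDs. Taking α = 0.05 as two-sided for a pairwise comparison (an assumption), 44 per group and 80% power imply a standardised difference of (1.960 + 0.842) × √(2/44) = 2.802 × 0.2132 = 0.597. That serves as the reference point below. The point does not depend on 132 or 152 being right.

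**Step 3. Effect on means.** Let a share p of patients use laxatives at entry, and let stopping lower their weekly count by d. The mean change in every arm shifts by −p·d:

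- p = 0.20, d = 1: −0.2 per week;
- p = 0.40, d = 2: −0.8 per week.

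The shift has the same expectation in each arm and cancels in the difference. The placebo arm, however, would then fall rather than stay unchanged, other things equal.

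**Step 4. Effect on power.** If users and non-users are mixed and the drop is independent of the rest of the change, the variance of change rises from SD² to SD² + p(1−p)d². With r² = (SD² + p(1−p)d²)/SD², power is Φ(2.802/r − 1.960). The SD of change without withdrawal is assumed to be 1.5 to 2.0 movements a week.

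| p | d | p(1−p)d² | SD | r² | r | Power |
|---|---|---|---|---|---|---|
| 0.20 | 1 | 0.16 | 1.5 | 2.41/2.25 = 1.071 | 1.035 | about 77% |
| 0.20 | 1 | 0.16 | 2.0 | 4.16/4.00 = 1.040 | 1.020 | about 78% |
| 0.40 | 2 | 0.96 | 1.5 | 3.21/2.25 = 1.427 | 1.194 | about 65% |
| 0.40 | 2 | 0.96 | 2.0 | 4.96/4.00 = 1.240 | 1.114 | about 71% |

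A wider grid (users 10–50%, drop 1–2 per week, SD 1.0–2.0) gives 51% to 79%. The width of that range shows how much depends on figures the documents do not supply.

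**Step 5. Breaches of the ban.** Section 2.6 withdraws patients who interrupt treatment but does not mention laxative use. Section 2.10 analyses by intention to treat. Movements that follow a prohibited laxative would therefore be counted as response. If breaches are commoner where constipation persists, the less effective arm gains more of these movements and the comparison moves toward no difference. The documents give no breach rate, so this cannot be sized.

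**The case against.** **Randomisation protects the comparison.** The planned tests are between arms, allocation is 1:1:1, and the ban covers everyone. A reader might infer from the mixed change score that the trial's treatment comparison is biased. The documents do not support that: withdrawal has the same expected effect in each arm. This part of the objection stands in full.

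**Some inferences go beyond the text.** A reader might also conclude that laxative users are sought out, that day 0 is always assisted, or that all movements are expressly counted. Need for laxatives is one of several features, and any two suffice. Where day 0 falls relative to the ban is not stated, and the schedule figure is not shown. The success value speaks of *effective* movements, which is ambiguous and not an explicit count of everything. Other forms named in sections 2.7 and 2.10 may record laxative use. So day 0 *can* be assisted, and counting all movements is the natural reading rather than a stated rule.

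**Adherence is checked.** Section 2.3 provides messages or calls, and section 2.6 a contact at 15 days. These may reduce or detect breaches, but nothing described links laxative use to the days counted. That breaches are commoner where constipation persists is an expectation, not something the documents show.

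**The power figures are soft.** All inputs are assumed. If the planning SD came from patients with a similar laxative mix, the variance is already in it. A drop of 2 also fits poorly with a baseline of 1 to 3 a week, since a patient at 1 cannot lose 2. And section 2.1 calls the placebo's contents a conventional treatment for constipation, which could offset a fall. These points limit the size of the effect but leave the gap in definition.

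**Conclusion.** The point holds as one of outcome definition and precision. Laxative users are eligible, no pre-entry laxative condition is stated, the ban starts with the trial, and the primary metric does not distinguish spontaneous from assisted movements. In current users the day 0 to day 30 change therefore mixes withdrawal with product effect. Attainment of the over-4-per-week value becomes less reliable, and the placebo arm need not stay flat as section 2.10 assumes.

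It does not follow that withdrawal biases the randomised difference. The cost there is variance: from 80% to about 77–78% in the milder scenario and 65–71% in the stronger one. Both rest on assumed values for the share of users, the drop and the SD, and on a planning SD that does not already include this variance. A pull toward no difference through breaches is plausible but conditional and unquantified.

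This should be changed: it touches the primary outcome, the remedy is cheap, and laxative use around day 0 is hard to recover reliably afterwards.

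**What to change.** 1. In section 2.4.1, define the primary frequency outcome at both time points as spontaneous bowel movements, meaning those that do not follow laxative use, with the time window stated. Use this in place of *effective*. It is the term section 2.2.1 already uses.
2. Add a daily yes/no laxative field to the diary, worded so that the study sachet does not count as a laxative. Movements after a breach can then be identified and are not counted as response.
3. Record laxative use at entry and adjust the between-arm comparison for it, for example as a factor in the ANOVA. If the drop is similar across users, this removes most of the added variance in step 4.
4. Reconcile sections 2.2.1, 2.2.2, 2.3 and 2.4.1 so that day 0 and day 30 are measured under a stated, comparable laxative condition. How that is achieved clinically is for the sponsor to decide.

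Cost: one diary column, one covariate and a short rewording of section 2.4.1.

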#### Active comparator: 3 billion CFU strains of probiotics

2.3.1

*Lactobacillus acidophilus* LA 02 ID 1688 1 billion CFU, *Bifidobacterium bifidum* BB 01 ID 1722 1 billion CFU, *Lactobacillus rhamnosus* LR 04 ID 1132 1 billion CFU, vitamin C (ascorbic acid) 45 mg, vitamin B1 (thiamine) 1.1 mg, vitamin B2 (riboflavin) 1.1 mg, vitamin D-3 40,000,000 IU/g (cholecalciferol) 34 mcg, magnesium hydroxide 0.3 g, calcium carbonate 0.5 g, natural vanilla flavor powder 0.03 g, Fos (fructooligosaccharides) qsp 3 g, for 30 days, once daily in the form of sachet.

Assigned interventions: Dietary supplement of fibers plus vitamins and minerals will be administered for 30 days once daily in sachets containing 3 billion CFU strains of probiotics

#### Active comparator: 8 billion CFU strains of probiotics

2.3.2

*Lactobacillus paracasei* LPC 00 ID 1076 1 billion CFU; *Bifidobacterium longum* BL 03 ID 1152 1 billion CFU; *Bifidobacterium lactis* BS 01 ID 1195 1 billion CFU; *Lactobacillus casei* LC 03 ID 1872 1 billion CFU; *Bifidobacterium animalis* LMG 10508 1 billion CFU*; Lactobacillus acidophilus* LA 02 ID 1688 1 billion CFU, *Bifidobacterium bifidum* BB 01 ID 1722 1 billion CFU, *Lactobacillus rhamnosus* LR 04 ID 1132 1 billion CFU, vitamin C (ascorbic acid) 45 mg, vitamin B1 (thiamine) 1.1 mg, vitamin B2 (riboflavin) 1.1 mg, vitamin D-3 40,000,000 IU/g (cholecalciferol) 34 mcg, magnesium hydroxide 0.3 g, calcium carbonate 0.5 g, natural vanilla flavour powder 0.03 g, Fos (fructooligosaccharides) qsp 3 g, for 30 days, once daily in the form of sachet

Assigned interventions: Dietary supplement of fibers plus vitamins and minerals will be administered for 30 days once daily in sachets containing 8 billion CFU strains of probiotics.

#### Placebo comparator: placebo

2.3.3

Vitamin C (ascorbic acid) 45 mg, vitamin B1 (thiamine) 1.1 mg, vitamin B2 (riboflavin) 1.1 mg, vitamin D-3 40,000,000 IU/g (cholecalciferol) 34 mcg, magnesium hydroxide 0.3 g, calcium carbonate 0.5 g, natural vanilla

Assigned interventions: Dietary supplement of fibers plus vitamins and minerals will be administered for 30 days once daily in sachets.

### Measured outcomes

2.4

#### Primary outcomes

2.4.1

Changes in the frequency of bowel movements and in stool quality will be noted down in a table which the patient must fill out with information about daily frequency and type of stool (on a scale of 1–7 of the Bristol scale, or whether there was no bowel movement).

Stool form will be assessed using the BSFS (Bristol Stool Form Scale), a simple tool for estimating intestinal transit time.^[5]^ The BSFS classifies stools into 7 categories, including type 1, separate hard lumps, like nuts; type 2, sausage-shaped, but lumpy; type 3, like a sausage but with cracks on the surface; type 4, like a sausage or snake, smooth and soft; type 5, soft blobs with clear-cut edges; type 6, fluffy pieces with ragged edges, a mushy stool; type 7, watery, no solid pieces.^[5]^ These types are categorized into slow transit (types 1 and 2), normal transit (types 3–5), and fast transit (types 6 and 7).

The metric of analysis will be the comparison between 0 and 30 days, considering that the number of effective bowel movements over 4 times a week is an effective value for the treatment and the quality of the stools from 3 to 5.

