**Methods:**

: A single-centre trial of adults aged 20 to 80 years with intestinal constipation will be conducted at a Gastroenterology Clinic in Sorocaba, State of São Paulo, Brazil. Participants will be allocated into 3 groups receiving:

The outcomes of interest will be change in frequency of weekly bowel movements, change in stool quality according to the 4–6 Bristol scale, number of volunteer withdrawal, number of adverse events and number of serious adverse effect.

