**Discussion::**

The probiotic products are expected to induce beneficial changes in the intestinal microbiota, thereby increasing intestinal frequency to over 3 times a week and improving stool quality. The results can guide patients and healthcare practitioners and help in decision-making in the treatment of functional constipation.

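### The primary stool-quality outcome has two incompatible Bristol target ranges (4–6 and 3–5), and no analysis named in section 2.10 tests the share reaching either

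*Protocol article*

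**What the plan says.** The protocol article gives the stool-quality target in two places:

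- **Abstract, Methods.** Among the outcomes of interest is "change in stool quality according to the 4–6 Bristol scale".
- **Section 2.4.1, Primary outcomes.** The metric compares day 0 with day 30, and success is set at "over 4 times a week is an effective value for the treatment and the quality of the stools from 3 to 5". The same section treats types 1 and 2 as slow and then lists "normal transit (types 3–5), and fast transit (types 6 and 7".

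For bowel frequency, the abstract's Discussion expects the products to act by "increasing intestinal frequency to over 3 times a week and improving stool quality". Section 2.10 states the hypothesis as a rise from 1–3 to over 4 a week, in line with section 2.4.1.

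On analysis, section 2.10 assigns continuous variables to ANOVA, and adverse events and the remaining outcomes to the t test and Mann–Whitney U. It adds: "Score changes between the intervention and the control groups will be compared by Kruskall–Wallis".

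**The concern.** Stool quality is a primary outcome, and its target range differs between two current parts of the same document. A participant who ends at type 3 succeeds under section 2.4.1 and fails under the abstract. A participant who ends at type 6 does the reverse. With both ranges in print, the one reported could be chosen after the results are seen.

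The analysis section does not settle the matter. Section 2.4.1 frames success as reaching a range in the middle of the scale, but none of the four tests named compares the share who reach it. Bristol type is the only scale in the protocol, so the natural reading is that the Kruskal–Wallis comparison of score changes applies to it. That test assumes that a larger change is better. On this scale benefit rises and then falls, so the test can credit an arm for stools that section 2.4.1 puts outside its own target.

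**Working it through.** **1. The ranges side by side**

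| Bristol type | Transit class (2.4.1) | Target 3–5 (2.4.1) | Target 4–6 (abstract) |
|---|---|---|---|
| 1, 2 | slow | no | no |
| 3 | normal | **yes** | **no** |
| 4, 5 | normal | yes | yes |
| 6 | fast | **no** | **yes** |
| 7 | fast | no | no |

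The 3–5 range coincides with the document's normal-transit class. The 4–6 range leaves out one normal type and takes in one fast type.

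**2. What ranking raw change does**

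From a baseline of type 2, ending at type 4 is a change of +2, at type 6 +4 and at type 7 +5. Kruskal–Wallis ranks them in that order. Under 3–5 only the first is a success.

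**3. Can the choice change the result?**

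The protocol gives no Bristol distributions, so the counts here are invented. The arm size of 44 comes from section 2.5. For simplicity there are two arms, one final type per participant, and every baseline is set to type 2.

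| Final type | 1 | 2 | 3 | 4 | 5 | 6 | 7 |
|---|---|---|---|---|---|---|---|
| Active | 2 | 4 | 4 | 10 | 9 | 13 | 2 |
| Placebo | 2 | 6 | 18 | 10 | 6 | 2 | 0 |

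The test is z = (p₁ − p₂) / √[p̄(1 − p̄)(2/44)], which is the chi-square test without continuity correction.

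- **Range 3–5.** Active 4 + 10 + 9 = 23 (52%); placebo 18 + 10 + 6 = 34 (77%). p̄ = 57/88 = 0.648, SE = 0.102, z = −0.250/0.102 = −2.45, p = 0.014, favouring placebo.
- **Range 4–6.** Active 10 + 9 + 13 = 32 (73%); placebo 10 + 6 + 2 = 18 (41%). p̄ = 50/88 = 0.568, SE = 0.106, z = 0.318/0.106 = 3.01, p = 0.003, favouring active.
- **Kruskal–Wallis on change.** H = 13.4, p = 0.0003, towards higher types in the active arm.

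Hard stools (types 1–2) are similar in the two arms, 6 active and 8 placebo. Types 6–7 are 15 against 2. Here the rank test responds largely to loose stools, not to relief of hard ones.

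**4. Frequency**

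The two cuts differ only for a participant with exactly 4 movements a week. If weekly counts were Poisson (an assumption) with mean 3, 4 or 5, success would be 35%, 57% or 73% for over 3, and 18%, 37% or 56% for over 4. The cuts are nested: everyone above 4 is also above 3.

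**The case against.** A reader might infer that both primary outcomes carry contradictory success thresholds. The document supports this only for stool quality. The figure of over 3 a week is an expected result in the abstract's Discussion, not a success criterion, and sections 2.4.1 and 2.10 agree on over 4. The abstract wording is a loose end.

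A reader might also infer that the trial's data will give opposite conclusions depending on the page followed. That is not shown. Take a milder assumed case of 50% active against 55% control in types 3–5, and 54% against 42% in types 4–6, with 44 per arm. The p-values are about 0.64 and 0.26: the sign changes, but neither result is significant. Only the deliberately built counts give a significant reversal.

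Three further points stand in part:

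- If only the tests named in section 2.10 produce the primary p-value, changing the range does not move it. That is true, but then the effective values in section 2.4.1 have no analysis, so the two sections still need to be joined.
- The document calls Bristol grades types, not scores, so applying Kruskal–Wallis to them is an inference, though the natural one. Frequency probably falls under ANOVA.
- A shift towards higher types can reflect fewer hard stools, which is a benefit in constipation. Suppose the milder case has 32% active against 10% control in types 6–7. Hard stools are then 100 − 50 − 32 = 18% against 100 − 55 − 10 = 35%, so a rank test favouring active would mix relief of hard stools with excess loose ones. The test is ambiguous rather than always misleading.

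**Conclusion.** The concern holds for stool quality. The two target ranges are incompatible on the printed text, with no assumption needed. Section 2.10 names no analysis of the share reaching the target, again on the printed text. That the rank test can favour an arm for stools outside the target depends on reading score changes as Bristol changes.

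The size is a possibility, not an estimate. With 44 per arm, one invented data set moves from 52% against 77% (p = 0.014, placebo better) to 73% against 41% (p = 0.003, active better) on the change of range alone. No probability can be attached to this, because the protocol gives no distribution of Bristol types. The frequency mismatch is minor and editorial.

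**What to change.** Before unblinding:

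1. Reconcile the abstract's Methods with section 2.4.1 to one Bristol range. The body text and its transit classes use 3–5.
2. Align the frequency wording in the abstract's Discussion with sections 2.4.1 and 2.10.
3. State in section 2.10 that the primary stool-quality comparison is the proportion in that range at day 30 against day 0. Compare arms with a method suited to proportions, for example logistic regression with arm and baseline, in place of Kruskal–Wallis on raw Bristol change.
4. Report types 6–7 separately, so that a shift to loose stools is visible.

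The diary already records daily stool type, so no new data are needed. How several diary stools are reduced to one value per participant can be left to the analysis plan. The cost is protocol wording and a few lines of code, and possibly a less favourable success rate than the other range would have given.
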